## **Clinician Post-Visit Fidelity Assessment Form** (To be distributed to clinicians following a visit with an enrolled FCP)

As part of your participation in the “Enhancing Dementia Instruction in Home Hospice Care (EDITH-HC)” study, please answer the following questions.

1. Please explain the main purpose of your visit on [insert date] with [insert patient name]?
2. [Control arm only] Please choose the option that best describes your interaction with [insert enrolled FCP name].
   1. We discussed what was happening with the patient.
   2. We discussed what was bothering the family member.
   3. We discussed what was happening with the patient and what was bothering the family member.
   4. I did not speak with the family member.
   5. Other (please explain)
3. [Intervention arm only] Please choose the option that best describes your interaction with [insert enrolled FCP name].
   1. The family member completed the [assessment tool/worksheet]] with some guidance from me.
   2. The family member completed the [assessment tool/worksheet]] with a lot of prompting from me.
   3. We completed the [assessment tool/worksheet]] together, making equal contributions.
   4. I left the [assessment tool/worksheet]] with the family member to complete on their own.
   5. I used the [assessment tool/worksheet]] as a guide, but did not complete it with the family member.
   6. We discussed what was bothering the family member, but I did not use the [assessment tool/worksheet]].
   7. I met with the family member, but we did not discuss what was bothering him/her.
   8. I did not speak with the family member during the visit.
   9. Other (please explain)
4. [Intervention arm only, if 3 d-f] Why didn’t you use the [assessment tool/worksheet] with the family member?
   1. I did not know I was supposed to do this.
   2. I forgot.
   3. I didn’t have a copy with me.
   4. There was not time to use it during the visit.
   5. The family member was not open to using the [tool/worksheet].
   6. This wasn’t an appropriate visit for the [tool/worksheet] to be used
   7. Other (please explain)
5. [intervention arm only if 3 a-c] Did you have any issues using the [assessment tool/worksheet] with the family member?
   1. No
   2. Yes (please explain)
6. [Intervention arm only, if 3 a-c] What challenge or concern did the family member identify? [text box]
7. [Intervention arm only] Did you record family member burden in the electronic hospice record following your visit?
   1. Yes
   2. No
8. [Intervention arm only if 6 b] Why didn’t you record family member burden in the electronic hospice record?
   1. I did not know I was supposed to do this.
   2. I do now know how to do this.
   3. I forgot.
   4. I did not have time.
   5. This wasn’t an appropriate visit for me to ask questions related to burden
   6. Other (please explain)
9. [Intervention arm only if 6 a]. Did you have any issues recording family member burden in the electronic hospice record?
   1. No
   2. Yes (please explain)
10. Additional comments or explanation.

| ***Table 2. Additional Feasibility and Fidelity Measures*** |  |
| --- | --- |
| **Feasibility and Fidelity Items** | **Measurements** |
| 1. Accrual rates | Number of potential participants contacted,  Percent of contacted enrolled  Number enrolled |
| 2. Attrition rates | Number enrolled,  Number and percent dropped out |
| 3. Adherence to the study protocol | Number and percent of clinicians:  1. viewing3 or more of the videos,  2. viewing more than 80% of each video,  3. using the tool more than 75% of the time,  4. number and percent of family care partners using the tool,  5. number of times family care partners are using the tool |
| 4. Number of educational video views | Total number of views,  Total number of unique viewers |
| 5. Frequency of issues related to viewing videos | Number of times clinicians report issues watching the video |
| 6. Types of issues related to viewing videos | Issues described by clinicians |
| 7. Number of assessment tool initial uses | Number of care partners with whom clinicians use the tool |
| 8. Number of assessment tool follow-up uses | Number of times clinicians use the tool as a follow-up |
| 9. Frequency of issues using assessment tool | Number of times clinicians report issues using the tool,  Number of times family care partners report issues using the tool |
| 10. Types of issues using assessment tool | Types of issues described by clinicians,  Types of issues described by family care partners |
| 11. Number of EHR burden reports | Number of times family care partner burden is recorded in the EHR from enrolled care partners |
| 12. Frequency of issues using EHR burden reports | Number of times clinicians report burden in the EHR |
| 13. Types of issues using EHR burden reports | Types of issues clinicians report recording burden in the EHR |
| 14. Number of clinicians using assessment tool | Number and percent of enrolled clinicians using the assessment tool |
| 15. Number of FCP with whom assessment tool is used | Number and percent of enrolled family care partners using the assessment tool as reported by family care partners and clinicians |
| 16. Number of data collection points with FCP | Total number of data collection points with family care partners  Average number of data collection points with family care partners (0-4),  Percent of family care partners with complete data for their hospice experience |
| 17. Frequency of issues completing data collection with FCP | Number of times issues with data collection are recorded for family care partners |
| 18. Types of issues with completing data collection with FCP | Types of issues with data collection recorded for family care partners |
| 19. Number of successful post-intervention surveys with clinicians | Number and percent of enrolled clinicians completing post intervention survey |
| 20. Frequency of issues completing post-intervention surveys with clinicians | Number of times with data collection that are recorded for clinicians |
| 21. Types of issues with completing post-intervention surveys with clinicians | Types of issues with data collection recorded for clinicians |

# Aim 3. Clinician assessment tools (Pre/Post, intervention and control)

***Dementia knowledge assessment scale***

Annear, M. J., Toye, C. M., Eccleston, C. E., McInerney, F. J., Elliott, K. E. J., Tranter, B. K., ... & Robinson, A. L. (2015). Dementia knowledge assessment scale: development and preliminary psychometric properties. *Journal of the American Geriatrics Society*, *63*(11), 2375-2381.

| **Q #** | **Statements about dementia** | **Response scale**  (Please tick one box ) | | | |  |
| --- | --- | --- | --- | --- | --- | --- |
|  |  | **False** | **Probably false** | **Probably true** | **True** | **I don’t know** |
| A1 | Dementia is a normal part of the ageing process. |  |  |  |  |  |
| A2 | Alzheimer’s disease is the most common form of dementia. |  |  |  |  |  |
| A3 | People can recover from the most common forms of dementia. |  |  |  |  |  |
| A4 | Dementia does **not** result from physical changes in the brain. |  |  |  |  |  |
| A5 | Planning for end of life care is generally **not** necessary  following a diagnosis of dementia. |  |  |  |  |  |
| A6 | Blood vessel disease (vascular dementia) is the most common form of dementia. |  |  |  |  |  |
| A7 | Most forms of dementia do **not** generally shorten a person’s life. |  |  |  |  |  |
| A8 | Having high blood pressure increases a person’s risk of developing dementia. |  |  |  |  |  |
| A9 | Maintaining a healthy lifestyle does **not** reduce the risk of  developing the most common forms of dementia. |  |  |  |  |  |
| A10 | Symptoms of depression can be mistaken for symptoms of dementia. |  |  |  |  |  |
| A11 | Exercise is generally beneficial for people experiencing  dementia. |  |  |  |  |  |
| A12 | Early diagnosis of dementia does **not** generally improve quality of life for people experiencing the condition. |  |  |  |  |  |
| A13 | The sudden onset of cognitive problems is characteristic of  common forms of dementia. |  |  |  |  |  |
| A14 | It is impossible to communicate with a person who has advanced dementia. |  |  |  |  |  |
| A15 | A person experiencing advanced dementia will **not** generally  respond to changes in their physical environment. |  |  |  |  |  |
| A16 | It is important to correct a person with dementia when they are confused. |  |  |  |  |  |
| A17 | People experiencing advanced dementia often communicate through body language. |  |  |  |  |  |
| A18 | Uncharacteristic behaviours in a person experiencing dementia are generally a response to unmet needs. |  |  |  |  |  |
| A19 | Medications are the most effective way of treating behavioural symptoms of dementia. |  |  |  |  |  |
| A20 | People experiencing dementia do **not** generally have problems making decisions. |  |  |  |  |  |
| A21 | Movement is generally affected in the later stages of dementia. |  |  |  |  |  |
| A22 | People with advanced dementia may have difficulty  speaking. |  |  |  |  |  |
| A23 | People experiencing dementia often have difficulty learning new skills. |  |  |  |  |  |
| A24 | Difficulty eating and drinking generally occurs in the later stages of dementia. |  |  |  |  |  |
| A25 | Daily care for a person with advanced dementia is effective when it focuses on providing comfort. |  |  |  |  |  |

**DKAS total scoring**

Step one: In your database, DKAS response categories should be labelled as follows:

False 1

Probably false 2

Probably true 3

True 4

I don’t know 5

Step two: Enter DKAS data.

Step three: Recode responses to ‘false’ statements and apply scoring system. The DKAS scoring system is as follows:

 Score 2 points for an answer of ‘true’ to a truthful statement.

 Score 2 points for an answer of ‘false’ to an untrue statement.

 Score 1 point for an answer of ‘probably true’ to a truthful statement.

 Score 1 point for an answer of ‘probably false’ to an untrue statement.

 Score 0 points for an answer of ‘true’ or ‘probably true’ to an untrue statement.

 Score 0 points for an answer of ‘false’ or ‘probably false’ to a truthful statement.

 Score 0 points for an answer of ‘I don’t know’.

Step four: Sum items to provide a total score. The maximum total score on the DKAS v2.0 is **50**.

Step five: To calculate subscale scores, sum the items for each subscale (see Annear et al. 2017 for subscale items). In order to compare the subscales, you may wish to standardize each subscale to a maximum of 1.

# Aim 3. FCP assessment tools (baseline, follow-up visits 2-4, intervention and control)

***Terminal Illness Acceptance***

1. Describe your loved one’s current health status

□ Relatively healthy

□ Seriously but not terminally ill

□ Seriously and terminally ill

***General Preparedness***

2. To what extent do you feel prepared for your loved one’s death? (Herbert, et al 2006 REACH study)

□ Not at all

□ Somewhat

□ Very much

***Self-Administered Caregiving Self-Efficacy Scale (CSES-8)***

We are interested in how sure you are that you can keep up your own activities and also respond to caregiving situations for your care partner (the person you care for). For each of the following questions, please ***circle*** the number that corresponds **how sure** you are that you can do the tasks regularly **at the present time**.

| 1. How sure or confident are you that you can ask a friend/family member to stay with your care partner for a day when you need to see the doctor yourself? | ________________________________  Not at all \| \| \| \| \| \| \| \| \| \| Totally  confident 1 2 3 4 5 6 7 8 9 10 confident |
| --- | --- |
| 2. How sure or confident are you that you can stop yourself from thinking about unpleasant aspects of taking care of your care partner? | ________________________________  Not at all \| \| \| \| \| \| \| \| \| \| Totally  confident 1 2 3 4 5 6 7 8 9 10 confident |
| 3. How sure or confident are you that you can stop yourself from worrying about future problems that might come up with your care partner? | ________________________________  Not at all \| \| \| \| \| \| \| \| \| \| Totally  confident 1 2 3 4 5 6 7 8 9 10 confident |
| 4. How sure or confident are you that you can cope with unexpected or new situations that may come up with your care partner? | ________________________________  Not at all \| \| \| \| \| \| \| \| \| \| Totally  confident 1 2 3 4 5 6 7 8 9 10 confident |
| 5. How sure or confident are you that you can do the things necessary to keep your stress under control? | ________________________________  Not at all \| \| \| \| \| \| \| \| \| \| Totally  confident 1 2 3 4 5 6 7 8 9 10 confident |
| 6. How sure or confident are you that you can do the things necessary to take care of your own health? | ________________________________  Not at all \| \| \| \| \| \| \| \| \| \| Totally  confident 1 2 3 4 5 6 7 8 9 10 confident |
| 7. How sure or confident are you that you can find resources in the community (meals, legal, support groups, etc.) that can help you take care of yourself and your care partner? | ________________________________  Not at all \| \| \| \| \| \| \| \| \| \| Totally  confident 1 2 3 4 5 6 7 8 9 10 confident |
| 8. Sometimes prevent your care partner from becoming angry or disruptive? | ________________________________  Not at all \| \| \| \| \| \| \| \| \| \| Totally  confident 1 2 3 4 5 6 7 8 9 10 confident |

***Preparedness Scale of the Family Care Inventory***

We know that people may feel well prepared for some aspects of giving care to another person, and not as well prepared for other aspects. We would like to know how well prepared you think you are to do each of the following, even if you are not doing that type of care now.

|  | Not at all prepared | Not too well prepared | Somewhat well prepared | Pretty well prepared | Very well prepared |
| --- | --- | --- | --- | --- | --- |
| 1. How well prepared do you think you are to find out about and set up services for him or her? | 0 | 1 | 2 | 3 | 4 |
| 1. How well prepared do you think you are for the stress of caregiving? | 0 | 1 | 2 | 3 | 4 |
| 1. How well prepared do you think you are to take care of his or her emotional needs? | 0 | 1 | 2 | 3 | 4 |
| 1. How well prepared do you think you are to find out about and set up services for him or her? | 0 | 1 | 2 | 3 | 4 |
| 1. How well prepared do you think you are for the stress of caregiving? | 0 | 1 | 2 | 3 | 4 |
| 1. How well prepared do you think you are to make caregiving activities pleasant for both you and your family member? | 0 | 1 | 2 | 3 | 4 |
| 1. How well prepared do you think you are to respond to and handle emergencies that involve him or her? | 0 | 1 | 2 | 3 | 4 |
| 1. How well prepared do you think you are to get the help and information you need from the health care system? | 0 | 1 | 2 | 3 | 4 |
| 1. Overall, how well prepared do you think you are to care for your family member? | 0 | 1 | 2 | 3 | 4 |

Is there anything specific you would like to be better prepared for?__________________________________________________________________________________ __________________________________________________________________________________________________________________________________________________________________________ _____________________________________________________________________________________

MEAN SCORE of the number of items answered: ___________

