##### 3. Study design

This study proposes to develop and pilot test a two-part intervention, Enhancing Dementia Instruction and Tool in Home Hospice Care (EDITH-HC), that provides 1) educational videos for hospice nurses and social workers (clinicians) about dementia-specific end-of-life care and 2) an assessment tool for clinicians to use as part of their clinical practice to use with FCP to identify and address dementia-related stressors for FCP of home hospice PLwD. This study will use a mixed-methods design including intervention refinement and pilot testing. To achieve **Aim 1** we will obtain 2 rounds of structured, key stakeholder input from 10 FCP, 5 hospice clinicians, and 5 research/content experts. We will use this input to refine training materials and a tool for clinicians. The training and tool will help home hospice clinicians identify and suggest tailored strategies to address common and distressing challenges for PLwD and FCP. For **Aim 2**, we will test the training and tool with 1-2 clinical teams of 8-12 hospice clinicians and 10 Black and white FCP to determine feasibility and acceptability. We will revise the training and tool based on feedback. For **Aim 3** we will conduct a randomized pilot study to determine the feasibility and acceptability of implementing the training and tool in clinical practice compared to usual care. We will also determine preliminary efficacy of the training and tool. Outcomes include: feasibility and acceptability of the intervention, improving clinician knowledge and confidence (*secondary outcomes*), reducing FCP burden (*primary outcome*), and increasing FCP preparedness and self-efficacy, and decreasing PLwD hospice disenrollment *(secondary outcomes)*.

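### As printed in the protocol, the Preparedness Scale form repeats two of its questions, and its mean-score rule gives them double weight

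*Protocol*

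**What the plan says.** The Protocol appendix, under Aim 3 FCP assessment tools, reproduces the "Preparedness Scale of the Family Care Inventory". The form goes to care partners in both arms at baseline and at follow-up visits 2 to 4. Each row is scored 0 to 4. The rows run in this order:

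- Row 1: "How well prepared do you think you are to find out about and set up services for him or her"
- Row 2: "How well prepared do you think you are for the stress of caregiving"
- Row 3: "How well prepared do you think you are to take care of his or her emotional needs"
- Row 4: the row 1 question again, in identical wording
- Row 5: the row 2 question again, in identical wording
- Row 6: "How well prepared do you think you are to make caregiving activities pleasant for both you and your family member"
- Row 7: "How well prepared do you think you are to respond to and handle emergencies that involve him or her"
- Row 8: getting help and information from the health care system
- Row 9: overall preparedness to care for the family member

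The form ends with its scoring rule, "MEAN SCORE of the number of items answered". Nothing says that a repeated row is to be dropped, merged or ignored.

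Section 3 (Study design) names "increasing FCP preparedness and self-efficacy" among the secondary outcomes. The hypotheses for the Aim 3 pilot trial place preparedness among the exploratory outcomes. Section 9 (Analytic Methods) lists it with the measures collected so that the right outcome can be identified for a fully powered trial.

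**The concern.** A scale scored as a simple mean is meant to give each question one share. Here two questions have two shares each, so the protocol, followed as written, yields a score that leans on services and stress. Because the denominator is the number of items answered, a care partner who sees a question for the second time and skips it is scored with different weights from one who answers it twice. The same person can also be weighted differently from one visit to the next.

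That matters because Section 9 plans to compare each person's responses at baseline and later. It also gives the collection of normative data and the choice of a future outcome as purposes of the pilot. A score whose weights depend on how many repeats were answered serves neither purpose well.

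**Working it through.** The protocol gives no figure for this scale, so there is nothing to reproduce. The check uses the printed rows and the printed scoring rule.

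**Count.** Nine rows. Services appears at rows 1 and 4, and stress at rows 2 and 5; the other five questions appear once each. Distinct questions: 9 − 2 = 7.

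**Weights with all nine rows answered.** Services 2/9 = 22.2%, stress 2/9 = 22.2%, each other question 1/9 = 11.1%. Services and stress together: 4/9 = 44.4%.

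**Comparator.** The source item list is not in the protocol, so the intended weight of this pair has to be assumed:

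- Seven printed questions, each counted once: 2/7 = 28.6%.
- One displaced item restored, giving eight: 2/8 = 25.0%.
- Both repeats standing where other items belong, giving nine: 2/9 = 22.2%.

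A one-category gain on services and stress alone therefore moves the printed score by 0.44. It would move the score by 0.29, 0.25 or 0.22 under these three assumptions.

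**Effect on one person's score.** Let a be the answer to services and to stress, and b the answer to each of the other five questions.

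- As printed: (4a + 5b)/9.
- Each printed question once: (2a + 5b)/7.
- Difference: (4/9 − 2/7)(a − b) = (10/63)(a − b) = 0.159(a − b).
- The largest possible size, when a and b differ by 4, is 4 × 0.159 = 0.63 on the 0 to 4 scale.

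**Effect of skipping.** Take a = 1 and b = 3. With all nine rows answered, the score is (4 + 15)/9 = 19/9 = 2.11. With both repeats skipped, it is (2 + 15)/7 = 17/7 = 2.43. If the person answers the repeats at one visit and skips them at another, the score moves by 0.32 although no answer has changed. If only one repeat is skipped, the pair carries 3/8 = 37.5%.

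**Between arms.** If the intervention shifts the pair by d and every other question by e, the expected difference is (4d + 5e)/9 as printed and (2d + 5e)/7 with each question once. Both are zero when d = e = 0. Repeating the rows in both arms therefore does not create a difference where none exists, provided repeats are skipped equally often in each arm.

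**The case against.** The best defence is that this may be a copying slip confined to the appendix. Data are collected by phone or electronic survey and held in a database such as REDCap, and the protocol does not show the operational form. This stands in part: the point concerns the form as printed, and whether care partners were asked the repeats has to be checked. A fault of text extraction cannot be wholly excluded, since the row numbers are garbled. It is unlikely, because the repeats are complete rows with their own response codes, and the emotional-needs row separates the first pair from the second.

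It can also be said that scoring belongs in the analysis plan, which is not at hand. But the protocol prints both the form and a scoring rule, and together they give a mis-weighted score. A later rule could drop repeats; it could not recover an item that was never asked.

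Several stronger readings are tempting and not supported:

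- **That the form is demonstrably not the named scale.** Verbatim repeats make a faithful copy unlikely. Without the source item list, though, neither the correct item count nor any displaced item can be stated.
- **That the trial's treatment comparison is biased.** Both arms use the same form on the same timeline.
- **That inflated reliability spoils an analysis.** The protocol plans no reliability analysis of this scale. The reliability of 0.9 in Section 9 belongs to the power calculation for the Zarit burden score.
- **That the score is tilted toward what the tool teaches.** Stressors are the tool's subject, but setting up services is not described as such.
- **That respondent burden is material.** Two short extra questions are a small load.

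The appendix also holds a separate single item on preparedness for the loved one's death, so this scale is not the only preparedness measure.

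**Conclusion.** The point holds for the form as printed. Two of seven distinct questions appear twice, and the stated rule gives them 44% of the score when every row is answered. The comparison figure is 29% if the seven printed questions are the whole scale, 25% if one item was displaced and 22% if two were; which of these applies cannot be settled from the protocol. Against the seven-question score, one person's result can differ by up to 0.63 on the 0 to 4 scale, and uneven skipping of repeats can produce apparent change within a person.

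The consequence is limited to the validity and comparability of one outcome, called secondary in Section 3 and exploratory in the Aim 3 hypotheses. The primary Zarit burden outcome and its power calculation do not depend on it. It should still be corrected, because preparedness is among the measures meant to inform the choice of outcome for the next trial.

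**What to change.** 1. Check both the printed form and the operational form (phone script and electronic survey) against the source scale. Remove the repeated rows and restore any item they displaced.
2. If duplicates were collected, specify before analysis that each distinct question counts once, for example by the first response or by the average of the two. Either removes the double weight. Apply the same rule at every visit and in both arms.
3. Do not report the nine-row mean as the standard scale score. If an item was displaced and never asked, say so with the results.

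The cost is one form check, a minor amendment to the appendix and one scoring rule. The sample size and the primary analysis do not change.
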